14.2 Patience Information (D,F,E,I)…………………………………………………………………………..27

14.3 General Consent (D,F,E,I)……………………………………………………………………………….32

Study synopsis

| Sponsor / Sponsor-Investigator | [name], Department of Visceral Surgery and Medicine, Inselspital, Bern University hospital University of Bern, 3010 Bern |
| --- | --- |
| Study Title: | Impact of a specialised wound-closing team on surgical site infections: A  prospective observational clinical trial |
| Short Title/Study ID: | CLOT trial |
| Protocol Version and Date: | Version: 1 Date: 18.01.2017 |
| Trial registration: | ClinicalTrials.gov (as soon as ethical approval is obtained) |
| Study category and Rationale | Category A: Observational study without relation to the use of drugs or medical devices. The risk for the participant is minimal and the study provides no additional strain to the participant. |
| Background and Rationale: | Surgical site infection is a frequent complication after abdominal surgery. The wound closure is done at the end of the procedure when the attention of the entire team may be affected because of tiredness and reduced attention of the surgical team.  With this study we aim to test if an exchange of the surgical team by a specialised wound closure team may reduce the impact of surgical site infection. |
| Objective(s): | To assess the influence of a specialised wound closure team on surgical site infections. |
| Outcome(s): | Primary outcome: Incidence of surgical site infections 30 days postoperatively.  Secondary outcome: mortality at 30 days, fascial dehiscence at 30 days postoperatively, postoperative complications according to Clavien-Dindo. |
| Study design: | Prospective controlled, observational, interrupted time series, monocentric study (before and after study). |
| Inclusion/Exclusion criteria: | Inclusion criteria : Patients undergoing elective or emergent laparotomy  Exclusion criteria : Preexisting surgical site infection |
| Measurements and procedures: | The control arm consists of 580 patients from the previous StOP?-study.  580 patients will be recruited in the trial arm.  Every patient has a follow up of thirty days in line with the recording of Swissnoso (national surveillance for SSI). |
| Study Intervention: | The wound closure will be done by a specialised team including one trained surgeon and one student. |
| Control Intervention | The control group consists of the study population of the StOP?-study. In this population the wound closure was done by the operation team under supervision of the main surgeon. |
| Number of Participants with Rationale: | Total of participants: 1160 (580 trial group, 580 control group). |
| Study Duration: | 2x9 months |
| Study Schedule: | Month Year of First-Participant-In:1.3.2016  Month Year of Last-Participant-Out: 30.11.2017  (baseline = 2^nd^ arm from the STOP? trial 1.3.2016 – 30.11.2016;  Intervention: 1.3.2017 – 30.11.2017) |
| Investigator(s): | [name]. med. [name], Department of Visceral Surgery and Medicine, University hospital Bern (Inselspital), 3010 Bern |
| Study Centre(s): | University hospital Bern (Inselspital) |
| Statistical Considerations: | Sample size: The incidence of SSI after abdominal surgery in the department for Visceral Surgery and Medicine is 20%. The aim is to detect a reduction of the overall incidence rate of SSI from 20% to 14% after a follow-up of 30 days. We defined the level of significance at 5% and power of 80%, assuming normal approximation to binomial distribution requires 484 surgeries in each cell, thus 968 patients overall. In the ongoing StOP?-study we have a drop out and study refusal rate of maximal 20%. Thus, a total of 1160 participants (580 per arm) need to be included.  Duration: The average number of laparotomies from 8:00 AM to 5:30 PM from Monday to Friday per year are 720. The study schedule includes first 9 months in the control (baseline: 2^nd^ arm of the STOP? Study) and then 9 months in the intervention group.  Outcome parameters will be assessed the same way as in the ongoing StOP? Study. Thus, the results of the StOP? Study will be used as the control arm and the intervention arm will start after termination of the StOP? study. |
| Risk-Benefit statement / GCP Statement: | SSI infections are associated with increased morbidity and length of hospital stay. Patients with SSI after laparotomy or laparoscopy typically need bed-side reopening of the skin or administration of antibiotic therapy. Thus, prevention of SSI is of high interest.  The primary treatment of the patient is not affected by the trial. The change of the surgical team potentially may irritate and distract other personnel that is involved in the treatment of the patient. This may be of relevance during the initial phase of the study. The operation time may rise a little. A higher risk for the patient is not to be expected as long as communication within the surgical team assures that all relevant information is passed to the closure team. Conversely, exchange of team members is frequently done in clinical routine for both surgeons and nurses.  This study will be conducted in compliance with the protocol, the current version of the Declaration of Helsinki, the ICH-GCP or ISO EN 14155 (as far as applicable) as well as all national legal and regulatory requirements. |

Studienzusammenfassung

| Sponsor / Sponsor-Investigator | [name], Department of Visceral Surgery and Medicine, Inselspital, Bern University hospital University of Bern, 3010 Bern |
| --- | --- |
| Titel: | Impact of a specialised wound-closing team on surgical site infections: A  prospective observational clinical trial |
| Abkürzung: | CLOT trial |
| Protokollversion: | Version: 1 Date: 18.01.2017 |
| Kategorie | Kategory A: Beobachtungsstudie. Die Behandlung der Patienten wird nicht verändert.. |
| Rationale | Wundinfekte sind eine häufige Komplikation nach abdominalchirurgischen Eingriffen. Der Wundverschluss erfolgt zu einem Zeitpunkt an welchem das chirurgische Team unter Umständen nach einer langen Operation müde und weniger konzentriert ist. Mit dieser Studie soll geprüft werden ob durch die Einführung von einem Wundverschlussteam die Rate an Wundinfekten gesenkt werden kann. |
| Ziel: | Prüfen ob die Inzidenz von Wundinfekten durch die Einführung eines Wundverschlussteams verändert wird. |
| Endpunkte: | Primärer Endpunkt: Wundinfekte 30 Tage postoperativ.  Sekundäre Endpunkte: Mortalität, Fasziendehiszenz, Komplikationen 30 Tage postoperativ. |
| Studiendesign: | Prospektiv kontrollierte Beobachtungsstudie (vorher – nachher Studie). |
| Ein- Ausschlusskriterien: | Einschlusskriterien: Patienten welche sich einer Laparotomie unterziehen  Ausschlusskriterien: Vorbestehender Wundinfekt |
| Prozeduren | Wundinfektsurveillance gemäss Swissnoso 30 Tage postoperativ. |
| Intervention: | Der Wundverschluss wird durch ein spezialisiertes Wundverschlussteam (1 Chirurg und 1 Student/Assistenzarzt) durchgeführt. |
| Kontrollgruppe | Studienpopulation des zweiten Armes der StOP?-Studie. In dieser Population wurde der Wundverschluss durch das primäre Operationsteam durchgeführt. |
| Anzahl Teilnehmer: | Teilnehmer 1160 (580 Intervention, 580 Kontrolle). |
| Studiendauer: | 2x9 Monate |
| Zeitplan: | Kontrollgruppe 1.3.2016 – 30.11.2016 (=2. Arm der STOP? Studie)  Intervention: 1.3.2017 – 30.11.2017 |
| Studienleiter | [name]. med. [name], Department of Visceral Surgery and Medicine, University hospital Bern (Inselspital), 3010 Bern |
| Studienzentrum | Department für Viszerale Chirurgie und Medizin, Inselspital, Bern |
| Statistische Überlegungen: | Studienpopulation: Die Inzidenz von Wundinfekten nach abdomineller Chirurgie in der Klinik für Viszerale Chirurgie und Medizin, Inselspital Bern ist 20%. Das Ziel der Vorliegenden Studie ist zu prüfen ob durch die Intervention die Inzidenz von Wundinfekten auf 14% reduziert werden kann. Bei einer Signifikanz von 5% und einer Power von 80% ergibt sich eine Population von 484 Patienten pro Arm. Bei einer erwarteten Dropout Rate von 20% müssen 580 Patienten pro Arm eingeschlossen werden. Somit müssen gesamthaft 1160 in die Studie eingeschlossen werden. |
| Risiken / Nutzen: | Wundinfekte sind mit einer erhöhten Morbidität und Mortalität assoziiert. Einfache Massnahmen welche die Inzidenz von Wundinfekten reduzieren könnten sind somit von grossem Interesse. Die Einführung von spezialisierten Wundverschlussteams könnte die Inzidenz von Wundinfekten reduzieren da somit das primäre Operationsteam entlastet werden könnte.  Durch die Studie wird die primäre chirurgische Therapie nicht verändert. Es ist möglich, dass durch den Teamwechsel eine gewisse Unruhe und Ablenkung entsteht. Möglicherweise gibt es hierfür eine gewisse Gewöhnung im Verlauf der Studie. Teamwechsel stellen an sich nichts ungewöhnliches in der Chirurgie dar und wurden bisher nicht routinemässig sondern nur bei Bedarf durchgeführt. Für den Patienten sollte kein zusätzliches Risiko entstehen sofern nötige Information zwischen den beiden Teams weiter gegeben wird. |

Abbreviations

| ASR | Annual safety report |
| --- | --- |
| CEC | Competent Ethics Committee |
| CRF | Case Report Form |
| GCP | Good Clinical Practice |
| Ho | Null hypothesis |
| H1 | Alternative hypothesis |
| HFG | Humanforschungsgesetz (Law on human research) |
| HMG | Heilmittelgesetz |
| PI | Principal Investigator |
| SOP | Standard Operating Procedure |
| SSI | Surgical site infection |
| SNCTP | Swiss National Clinical Trials Portal |
| TMF | Trial Master File |
|  |  |
|  |  |
|  |  |
|  |  |
|  |  |
|  |  |

# STUDY ADMINISTRATIVE STRUCTURE

This trial is an investigator-initiated single-centre trial, initiated and coordinated by the Department of Visceral Surgery and Medicine, Bern University Hospital.

## Data Safety Monitoring Committee

A Data Monitoring Board will oversee the trial for any safety issues. A charter will be drafted before the first patient is included.

## Any other relevant Committee, Person, Organisation, Institution

None

# ETHICAL AND REGULATORY ASPECTS

The decision of the CEC concerning the conduct of the study will be made in writing to the Sponsor-Investigator before commencement of this study. The clinical study can only begin once approval from all required authorities has been received. Any additional requirements imposed by the authorities shall be implemented.

## Study registration

The study will be registered at clinicaltrials.gov. After obtaining the trial identification number the study will additional be registered at the Swiss National Clinical Trials Portal (SNCTP).

## Categorisation of study

Category A: Observational study without relation to the use of drugs or medical devices. The risk for the participant is minimal and the study provides no additional strain to the participant.

## Competent Ethics Committee (CEC)

The principal investigator ensures that the study will be approved by the local Competent Ethics Committee (Kantonale Ethikkommission Bern)

No changes are made to the protocol without prior Sponsor and CEC approval, except where necessary to eliminate apparent immediate hazards to study participants.

Premature study end or interruption of the study is reported within 15 days. The regular end of the study is reported to the CEC within 90 days, the final study report will be submitted within one year after study end.

## Ethical Conduct of the Study

The study will be carried out in accordance to the protocol and with principles enunciated in the current version of the Declaration of Helsinki, the guidelines of Good Clinical Practice (GCP) issued by ICH. The CEC will receive annual safety and interim reports and be informed about study stop/end in agreement with local requirements.

## Declaration of interest

The sponsor-investigator and the subinvestigators involved in the clinical trial declare no support from any organisation for the trial; no financial relationships with any organisations that might have an interest in the results of the trial; no other relationships or activities that could appear to have an influence on the trial.

## Patient Information

For this study no informed consent will be obtained because of the following reasons:

- Surgical site infections are assessed for surveillance according to the standards of Swissnoso. This is being performed as a routine surveillance and will not change during the study.
- The operation procedure in its technical aspect will not change during the intervention period. The only difference is another surgical team will be doing the wound closure. Therefore, the standard treatment of the patient during the intervention will not be altered compared to the control period.

An information sheet and a general consent form with explanation that we use their health-related data will be provided to all participants. Each participant will be informed that the participation in studies is voluntary and that he/she may withdraw from the general consent at any time and that withdrawal of consent will not affect his/her subsequent medical assistance and treatment.

The participant will be informed that his/her medical records may be examined by authorised individuals other than their treating physician.

The patient information sheet and the general consent form are attached (Appendix B). The formal consent of a participant, using the approved consent form, will be obtained before the participant is submitted to any study procedure.

The participant will read and consider the statement before signing and dating the general consent form, and is given a copy of the signed document. The consent form will be signed and dated by the investigator (or his designee).

## Participant privacy and confidentiality

The investigator affirms and upholds the principle of the participant's right to privacy and that they shall comply with applicable privacy laws. Especially, anonymity of the participants shall be guaranteed when presenting the data at scientific meetings or publishing them in scientific journals.

Individual subject medical information obtained as a result of this study is considered confidential and disclosure to third parties is prohibited. Subject confidentiality will be further ensured by utilising subject identification code numbers to correspond to treatment data in the computer files.

For data verification purposes, authorised representatives of the Sponsor-Investigator, the ethics committee may require direct access to parts of the medical records relevant to the study, including participants’ medical history.

## Early termination of the study

The Sponsor-Investigator may terminate the study prematurely according to certain circumstances, for example:

- ethical concerns,
- when the safety of the participants is doubtful or at risk, respectively,
- alterations in accepted clinical practice that make the continuation of a clinical trial unwise,
- early evidence of benefit or harm of the experimental intervention

## Protocol amendments

Substantial amendments are only implemented after approval of the CEC.

Under emergency circumstances, deviations from the protocol to protect the rights, safety and well-being of human subjects may proceed without prior approval of the sponsor and the CEC. Such deviations shall be documented and reported to the sponsor and the CEC as soon as possible.

All Non-substantial amendments are communicated to the CEC within the Annual Safety Report (ASR).

# Background and Rationale

## Background and Rationale

Incisional surgical site infection (SSI) is one of the most frequent complications after abdominal surgery, leading to considerable costs. we have shown that the performance of the surgical team impacts on SSI in addition to the patients pre-existing diseases ^1-3^. Pre-existing diseases of the patient mostly cannot be influenced. Therefore, we aim to optimize the performance of the surgical team in order to reduce SSI. Our data from observational studies reveal that discipline and communication within the surgical team impact on SSI^1,2,4^. With the proposed studies we now aim to address the aspect of fatigue on the performance of surgical team. The wound closure is done in a phase of the operation when concentration and motivation of the team often decreases. The exchange of the operation team (as described below in detail) represents a potential clinical applicable intervention that may improve SSI.

## Clinical Evidence to Date

We have observed that team behaviour and communication may impact on the outcome of abdominal surgery ^1,2,4^. Being the most frequent complication, surgical site infection has been used as the primary outcome parameter in these studies. The association of team behaviour and surgical site infection has been made in other surgical specialities^5-7^.

However, to alter the behaviour of the surgical team has been notoriously difficult. One attempt to impact on behaviour in the operating room was the introduction of checklists^8^. Despite being applied now in many hospitals, the success of such a measure highly depends on the education and dedication of the surgical team and failures have been described^9,10^. From team training interventions in other fields it is known that general team trainings often show limited effects^11^, whereas specific interventions are more promising ^12,13^.

With the proposed studies we now aim to overcome such behavioural risk by introducing a structural change within the process of wound closure. A specific closure team potentially should interpret the closure of the abdomen as their primary task, whereas for the first team closure has rather been a secondary task after a complex intraabdominal operation.

## Explanation for choice of comparator

The control group represents the current standard of care in which the same surgical team performs the wound closure.

In the trial group a trained team consisting of a surgeon and a student will replace the surgical team and will perform the closure of the laparotomy, irrigation of the wound and skin suturing.

We chose the design of a prospective controlled, two armed, observational study (before and after study). As the control group we will use the population of our ongoing STOP?-Study. Using this approach we have the opportunity to profit from the already established assessment of the clinical endpoint within the StOP? study that has been shown to be highly reliable.

## Risks / Benefits

The primary treatment of the patient is not affected by the trial. The change of the surgical team potentially may irritate and distract other personnel that is involved in the treatment of the patient. This may be of relevance during the initial phase of the study. The operation time may rise a little, however, a higher risk for the patient is not to be expected. Conversely, exchange of team members is frequently done in clinical routine for both surgeons and nurses.

## Justification of choice of study population

Included in the study are all patients (elective and emergency) with laparotomy and closure of the wound from Monday to Friday from 8:00 to 17:30 o clock. The time restriction is based on the difficulty to organize a team outside of regular working hours.

# STUDY OBJECTIVES

## Overall Objective

The aim of this trial is to test the impact of the exchange of the surgical team during wound closing on the incidence of SSI.

SSI is a frequent complication after laparotomy. Its incidence depends of the performance of the surgical team. Evidence revealed however, that the performance of the surgical team may be reduced at the end of the surgical procedure because of fatigue. By the exchange of surgical team members high quality of surgical performance may be maintained.

## Primary Objective

To assess the influence of a specialised wound closure team on the incidence of SSI 30 days after the operation.

## Secondary Objectives

To assess the influence of a specialised wound closure team on mortality, fascial dehiscence.and postoperative complications according to Clavien-Dindo.

# STUDY OUTCOMES

## Primary Outcome

SSI that occur after surgery will be assessed according to the criteria developed by the Centers for Disease Control and Prevention^14^. Infections will be categorized as incisional (superficial or deep) infections or organ–space infections. Superficial SSI (type 1) involve only skin and subcutaneous tissueand exclude stitch abscesses. Deep SSI (type 2) involve deeper soft tissues, like fascia and muscle, at the site of incision. Organ–space SSI (type 3) involve any organ or body cavity.

Incidence of SSI is assessed according to the clinical routine, following the established protocol of Swissnoso. Data collection according to the Swissnoso protocol will be extended to all surgeries included. The protocol includes direct contact to the patient:

- All patients receive a standardised follow-up phone call at least 30 days after the operation to assess incidence of SSIs and other complications.
- If patients do not respond to follow-up phone calls, five documented attempts to contact the patients followed by rapid contacts with the subject’s general practitioner or other medical staff involved in the medical treatment of the patients, will be performed before loss of follow-up is documented.

Surveillance according to Swissnoso is performed by the department of infectious diseases of the University hospital of Bern and are further supervised by external reviewers from Swissnoso. Therefore the observers are independent and evaluation bias is minimized.

## Secondary Outcomes

The assessment of postoperative mortality will be included to the telephone interview and assessed as follows:

Mortality at 30 days: Observer receives the information during the follow-up phone call that the patient died. If patients do not respond to follow-up phone calls, five documented attempts to contact the patients followed by rapid contacts with the subject’s general practitioner or other medical staff involved in the medical treatment of the patients, will be performed before loss to follow-up is documented. In addition, the Zivilstandsamt will be contacted once 3 months after surgery.

Postoperative fascial dehiscence at 30 days postoperative.

Complications: Assessment according to Clavien-Dindo grading

## Other Outcomes of Interest

In order to perform subgroup analyses or adjusted analyses, the following variables are assessed (Dokument 1 Swissnoso):

- - Type of operation (Haupteingriff, Sekundäreingriff)
  - Grade of contamination (Kontaminationsgrad)
  - Duration of the procedure
  - Height and weight of the patient.

# STUDY DESIGN

## General study design and justification of design

Prospective controlled, two armed, observational, monocentric study (before and after study).

To evaluate the impact of a specialised wound-closing team on surgical site infections

Included in the study are all patients (over 18 years, elective and emergency) with laparotomy and closure of the wound from Monday to Friday from 8:00 to 17:30 o’clock. We aim to include a total of 1785 participants.

The control group consists of the study population of the StOP?-study. In this population the wound closure was done by the same operation team under supervision of the main surgeon.

The screening of the first participant in the control group started on the 01.03.2016 and ended with the STOP? study on the 30.11.2016. The inclusion of patients in the intervention group takes place between 1.3.2017 and 30.11.2017. Therefore the end of data collection will be the 31.12.2017.

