# STUDY POPULATION

## Eligibility criteria

Participants fulfilling all of the following inclusion criteria are eligible for the study:

- General Consent as documented by signature (Appendix B)
- Patients undergoing elective or emergency laparotomy from Monday to Friday with wound closure from 8:00 until 17:30 and duration of operation.
- Age over 18 years
- Any indication for laparotomy

The presence of any one of the following exclusion criteria will lead to exclusion of the participant:

- Patients < 18 years of age
- Patients with preexisting SSI

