## Recruitment and screening

All patients with documented general consent undergoing elective or emergency laparotomy will be included in this study.

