## Assignment to study groups

The patients will be assigned to the study groups according to the time point of inclusion. In the period between 1.3.2016 to 30.11.2016 the control group was assessed. Patients operated between 1.3.2017 and 30.11.2017 represent the intervention group.

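### Controls are defined by study arm and dates, with no statement that the weekday 8:00–17:30 closure window is applied to them, so eligibility may change at the moment the intervention starts

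*Protocol*

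**What the plan says.** **Controls.** Section 6.1: "The control group consists of the study population of the StOP?-study". Section 3.3: "As the control group we will use the population of our ongoing STOP?-Study". The synopsis schedule limits them to the second "arm from the STOP? trial 1.3.2016 – 30.11.2016", and section 7.3 fixes the dates: "In the period between 1.3.2016 to 30.11.2016 the control group was assessed". The synopsis gives the number: "The control arm consists of 580 patients from the previous StOP?-study". These definitions use arm and calendar period. None uses time of day.

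**Window.** Section 7.1 lists as an inclusion criterion: "Patients undergoing elective or emergency laparotomy from Monday to Friday with wound closure from 8:00 until 17:30 and duration of operation". Sections 3.5 and 6.1 state the same hours for the study as a whole. Section 3.5 gives the only reason: "The time restriction is based on the difficulty to organize a team outside of regular working hours".

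**Places where the window is absent.** Section 7.2: "All patients with documented general consent undergoing elective or emergency laparotomy will be included in this study". The synopsis row on inclusion and exclusion criteria has no hours either. Section 10.4.2 describes the criteria as so broad that they take in nearly every operation except those done because of an SSI.

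**Protection against bias.** Section 6.2.3 relies on including every patient in both periods. Section 10.4.1 adjusts for type of surgery, NNIS score and age, with the aim of correcting chance imbalances.

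**The concern.** A before-after comparison is interpretable only if the same rule admits patients in both periods. Control enrolment ended on 30.11.2016 and the protocol is dated 18.01.2017. The window can therefore reach the controls in only two ways: StOP? already had it, or StOP? records are filtered afterwards. The protocol states neither and does not describe StOP? eligibility.

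If the existing StOP? arm is taken over as it stands, the baseline may contain evening, night and weekend closures that the intervention period excludes. Such a change falls exactly at the boundary between the periods, so an interrupted time series would read it as a level change due to the closure team. The defence in section 6.2.3 would then fail, because every patient would mean different patients before and after.

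The window has two further weaknesses. It is tied to wound closure, which follows the team exchange, and section 3.4 expects that operation time may rise slightly. The protocol does not say whether closure must start or end by 17:30. If the end counts, the intervention can itself affect who is eligible. The criterion also closes with a reference to duration of operation that has no threshold and cannot be applied.

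**Working it through.** **1. The plan's own control figure.** Inputs from section 10.2: 20% versus 14%, 5% significance, 80% power.

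n = [z_α·√(2p̄q̄) + z_β·√(p₁q₁ + p₂q₂)]² / d², with p̄ = 0.17 and d = 0.06.

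At one-sided 5%: (1.645 × 0.5312 + 0.842 × 0.5295)² / 0.0036 = 484 per arm, which reproduces the plan. (Two-sided 5% would give 615; that is a separate matter.) Then 484 × 1.2 = 580.8, stated as 580.

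**2. Expected in-window supply.** Section 10.2 gives 720 laparotomies per year within the window. Over nine months: 720 × 9/12 = 540.

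- Before losses: 580 − 540 = 40 short, or 40/580 = 6.9%.
- After the 20% loss that the plan allows: 540 × 0.8 = 432 against 484 needed, 52 short, or 52/484 = 10.7%.

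Step 1 shows that 580 comes from the sample-size formula, so it need not be a count of StOP? patients. The intervention arm has the same target from the same expected supply. The excess therefore does not show that out-of-window controls are present. It does mean that a reader cannot infer from the numbers that the window was applied to them.

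**3. What an unfiltered baseline could do.** The documents give neither the share f of controls closed outside the window nor their SSI risk ratio RR relative to in-window patients. Both are assumed. With an in-window risk of 20% and no true effect:

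Spurious difference D = 20% × f × (RR − 1).

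Chance of a significant result favouring the closure team = Φ[(D − 1.96·SE₀)/SE], with 484 per arm and an unadjusted two-sided 5% test (nominal 2.5% in each direction).

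Example, f = 20%, RR = 1.5: control risk 22%, D = 2.0 points, SE₀ and SE both 0.0262, so Φ[(0.020 − 0.0513)/0.0262] = 11.6%.

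| f | RR | D (points) | Falsely favours team | Falsely against team |
|---|---|---|---|---|
| 20% | 0.75 | −1.0 | 0.9% | 5.9% |
| 30% | 0.75 | −1.5 | 0.5% | 8.6% |
| 20% | 1.0 | 0 | 2.5% | 2.5% |
| 10% | 1.25 | +0.5 | 3.9% | 1.6% |
| 10% | 1.5 | +1.0 | 5.8% | 1.0% |
| 20% | 1.5 | +2.0 | 11.6% | 0.3% |
| 30% | 1.5 | +3.0 | 20.5% | 0.1% |
| 30% | 2.0 | +6.0 | 60.2% | 0.0% |

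The sign depends entirely on RR. The table is unadjusted, so the planned covariates would shrink these figures by an unknown amount.

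**4. What the covariates cover.** ASA score, contamination and duration (through the NNIS score), type of surgery and age would absorb part of any difference in case mix. Time of closure and elective or emergency status are not among the covariates named in section 10.4.1.

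**The case against.** The strongest reply is that the window is not written for one arm. Section 6.1 states it for the whole study in the paragraph directly before the sentence on controls, section 7.1 lists it for all participants, and section 10.2 uses one in-window volume to plan both periods. Read this way, an out-of-hours StOP? patient is simply ineligible. This stands in part: the defect is two provisions left unreconciled, not an explicit difference in criteria. It does not settle the matter, because the controls are an arm already enrolled and the synopsis says that the StOP? results will serve as the control arm.

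Silence in section 7.2 and the synopsis is weak evidence alone. Section 7.2 also omits the age limit and the exclusion for pre-existing SSI, and nobody would take those as waived.

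Three stronger readings are tempting, and the documents do not support them:

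- That the controls are the whole StOP? population. The synopsis, section 7.3 and section 10.2 confine them to the second arm and nine dated months.
- That the bias favours the closure team. This needs a higher SSI risk outside the window, and no figure by time of day is given.
- That 580 against 540 proves out-of-window controls. Loose planning or variation between years explains it equally well.

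StOP? may in fact have used the same hours. Its protocol is not part of these documents, so a mismatch is possible and not shown.

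**Conclusion.** The control definition and the eligibility rule are not reconciled, and the reader cannot tell which patients form the baseline. If the StOP? arm is used unfiltered, eligibility changes together with the intervention. The comparison could then be biased in either direction, and the planned adjustment would repair it only in part.

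Neither size nor sign can be derived from the documents. For an assumed out-of-window share of 10–30% and risk ratios of 0.75 to 1.5, the unadjusted distortion is between −1.5 and +3.0 points on a target of 6. If StOP? had the same window, or the filter is applied, this distortion is zero. The point should be settled before outcomes are compared, because selecting controls afterwards would be open to challenge. The unspecified time anchor and the unfinished clause on duration in section 7.1 are drafting defects that hold whatever StOP? did.

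**What to change.** - In sections 6.1 and 7.3, define the controls as StOP? second-arm patients operated on between 1.3. and 30.11.2016 who meet every criterion in section 7.1, selected from recorded times before outcomes are compared. If StOP? already used the window, say so.
- Define the window in both periods by one clock time that the team exchange cannot alter. The end of closure does not qualify, and the start of closure also falls after the exchange. The start of the operation is one candidate.
- Put the same window into section 7.2 and the synopsis inclusion row.
- Complete or delete the clause on duration of operation in section 7.1.
- Report the number excluded by each criterion in each period.

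**Cost.** Wording changes and one filter on existing records; section 11.1.2 says the StOP? database is reused. The sponsor must confirm that clock times were recorded in StOP?. The control group may become smaller. If both periods yield 432 analysable patients (540 × 0.8), power for 20% versus 14% is 76.0% one-sided or 65.1% two-sided, compared with 80.0% and 70.1% at 484 per arm.
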